### Intervention

All participants will first receive a standardized 30-min health education session covering sarcopenia, healthy lifestyle practices, and nutrition-related prevention strategies. Before intervention delivery, caregivers assigned to the exercise groups will undergo centralized training by exercise specialists to ensure standardized implementation across residential buildings. Usual medical care and routine nursing home services will continue throughout the trial in all groups. Participants will be asked not to initiate any additional structured exercise programme outside the study during the intervention period. Any relevant changes in health status, medication use, or rehabilitation participation will be documented where feasible.

To minimize contamination across groups, exercise sessions will be delivered within the assigned residential buildings and scheduled separately by group. Caregivers involved in intervention delivery will be assigned to specific buildings during scheduled sessions, and group-specific exercise materials will not be shared across groups. Participants will be asked not to attend sessions assigned to other groups. Any additional rehabilitation, structured exercise, or cross-group exposure will be recorded through caregiver logs, participant reports, and process evaluation activities [39].

The intervention is designed as a 48-week pragmatic, group-based exercise programme delivered within participants’ residential buildings. Exercise sessions will be conducted three times per week, with each 45-min session comprising a 10-min warm-up, a 30-min core exercise component, and a 5-min relaxation period. To enhance feasibility in routine nursing home care, the programme will be delivered using pre-recorded specialist-led videos and supervised through a phased model in which specialist involvement is progressively reduced and caregiver-led delivery correspondingly increased over time.

During weeks 1–12, specialists will provide on-site supervision for all sessions alongside caregivers. During weeks 13–24, on-site supervision will be reduced to one randomly scheduled visit per week, with the remaining sessions supported remotely. During weeks 25–48, sessions will be primarily supervised by caregivers using the video-guided materials, while specialists continue to provide remote oversight. Attendance at each scheduled exercise session will be recorded electronically by caregivers and summarized as an adherence and feasibility indicator; detailed attendance definitions and calculation procedures are provided in Additional file 1.

Adherence support will be guided by the Capability, Opportunity, Motivation–Behaviour (COM-B) model [40], and the Theoretical Domains Framework (TDF) [41] targeting exercise adherence in participants. Specifically, delivery within participants’ residential buildings, small-group sessions, caregiver assistance, and specialist supervision will target physical and social opportunity; health education, video-guided instruction, and seated exercise formats will target psychological and physical capability; and attendance monitoring, supportive feedback, low-value attendance-based incentives, and public recognition of highly engaged participants who consent to being acknowledged will target reflective and automatic motivation through reinforcement, self-efficacy, social norms, commitment, and habit formation [42].

Intervention sessions may be modified or temporarily discontinued for individual participants in the presence of acute illness, pain exacerbation, dizziness, chest discomfort, marked fatigue, participant refusal, or any other condition judged by caregivers or supervising staff to make continued exercise unsafe. Participants who discontinue the intervention will be encouraged to remain in outcome assessments whenever possible. Detailed intervention procedures are presented in Fig. 2 and Additional file 1.

**Fig. 2 Fig2:**
[figure not shown]
Overview of the 48-week intervention design, implementation timeline, and supervision strategy

#### Modified Baduanjin group

Participants in the modified Baduanjin group will perform a seated, safety-adapted programme developed for oldest-old nursing home residents with limited mobility and elevated fall concerns. The protocol retains the coordinative and mind–body characteristics of traditional Baduanjin while incorporating modifications intended to improve feasibility and lower-limb engagement in frail institutionalised older adults. Detailed exercise protocol and progression rules are provided in Additional file 1.

#### Resistance training group

Participants in the resistance training group will undertake an elastic-band programme targeting major upper- and lower-limb muscle groups relevant to functional mobility and daily activities. The programme is based on established recommendations for resistance exercise in older adults and incorporates progressive adjustment of training load according to participant tolerance and perceived exertion. Detailed exercise protocol and progression rules are provided in Additional file 1.

#### Combined exercise group

Participants in the combined exercise group will receive both modified Baduanjin and resistance training within the same session, with the aim of simultaneously targeting muscular strength, flexibility, and neuromuscular coordination. This combined format is intended to integrate the potential benefits of mind–body exercise and progressive resistance exercise within a feasible nursing home delivery model. To ensure time-matched comparability across groups, the combined exercise group will follow the same session duration and weekly frequency as the single-modality groups. The 30-min core exercise component will comprise approximately 15 min of modified Baduanjin and 15 min of resistance training.

#### Control group

Participants in the control group will attend the same standardized health education session at study initiation but will not receive any study-provided structured exercise during the 48-week intervention period. They will be asked to maintain their usual daily routines and will complete all scheduled assessments concurrently with the intervention groups.

### Outcome assessment

Outcome assessments are scheduled to evaluate both short-term intervention effects and the maintenance of longer-term benefits. With the exception of biospecimen collection, the outcomes will be assessed at baseline, weeks 12, 24, and 48, and again at 1-year and 2-year post-intervention follow-up. HG will additionally be measured every 4 weeks during the intervention period to capture more continuous changes in muscle strength, whereas biospecimens will be collected at baseline and week 48 only. The full assessment schedule is summarized in Table 1.

**Table 1 Tab1:** Schedule of study assessments

Measure	Screening	Baseline	Intervention												Follow-up	
		**Week 0**	**Week 4**	**Week 8**	**Week 12**	**Week 16**	**Week 20**	**Week 24**	**Week 28**	**Week 32**	**Week 36**	**Week 40**	**Week 44**	**Week 48**	**Year 1**	**Year 2**
Primary outcomes																
Sarcopenia Z-score	** × **	** × **			** × **			** × **						** × **	** × **	** × **
Components																
ASMI	** × **	** × **			** × **			** × **						** × **	** × **	** × **
HG	** × **	** × **	** × **	** × **	** × **	** × **	** × **	** × **	** × **	** × **	** × **	** × **	** × **	** × **	** × **	** × **
SPPB	** × **	** × **			** × **			** × **						** × **	** × **	** × **
Secondary outcomes																
TUG		** × **			** × **			** × **						** × **	** × **	** × **
PA level		** × **			** × **			** × **						** × **	** × **	** × **
sEMG		** × **			** × **			** × **						** × **	** × **	** × **
Balance function		** × **			** × **			** × **						** × **	** × **	** × **
Sample collection		** × **												** × **		
Questionnaires		** × **			** × **			** × **						** × **	** × **	** × **
Clinical events		** × **			** × **			** × **						** × **	** × **	** × **
Care-dependency		** × **			** × **			** × **						** × **	** × **	** × **

“ × ” indicates that the corresponding outcome measure or assessment will be conducted at that visit. Questionnaire-based assessments include the CMMS, MoCA, GDS-15, GAD-7, PSQI, CFS, SF-36, ADL scale, CCMQ, and ACE-based indicators. Repeated questionnaire assessments refer to time-varying domains; non-time-varying or historical variables, including demographic characteristics, educational attainment, family background, and adverse childhood experience indicators, will be collected at baseline only. Clinical events and care-dependency records include mortality, hospitalization or emergency transfer, falls, injurious falls, and care-dependency level, which will be continuously recorded during intervention and follow-up, and will be summarized at baseline, Week 12, Week 24, Week 48, and 1 and 2 years post-intervention

*ASMI* Appendicular Skeletal Muscle Mass Index, *HG* Handgrip Strength, *SPPB* Short Physical Performance Battery, *TUG* Timed Up and Go Test, *PA* Physical Activity, *sEMG* Surface Electromyography, *CMMS *Chinese Mini-Mental Status, *MoCA* Montreal Cognitive Assessment, *GDS-15* 15-item Geriatric Depression Scale, *GAD-7* Generalized Anxiety Disorder-7, *PSQI* Pittsburgh Sleep Quality Index, *CFS* Clinical Frailty Scale, *SF-36* 36-item Short Form Health Survey, *ADL* Activities of Daily Living, *CCMQ* Constitution in Chinese Medicine Questionnaire, *ACE* Adverse Childhood Experiences

All assessments will be conducted by trained research staff using standardized procedures, and outcome assessors will remain blinded to group allocation. To minimize participant burden, assessments will be arranged on residents’ residential floors whenever feasible. Portable and low-risk assessments will be conducted in residents’ rooms, whereas physical performance and device-based assessments will be completed in nearby familiar spaces under safety supervision. Non-time-varying or historical variables will be collected at baseline only. Rest breaks will be provided, and assessments may be split across short sessions, deferred, shortened, or omitted if participants experience fatigue, discomfort, or safety concerns. When the full assessment battery cannot be completed, primary outcome components and safety-related assessments will be prioritized, followed by key functional outcomes; exploratory mechanistic assessments, including sEMG, balance-board testing, and biospecimen collection, will be conducted only when safe and tolerated. Reasons for incomplete assessments will be documented.

#### Baseline characteristics

Baseline characteristics will be collected using a structured electronic questionnaire. Data will be obtained through individualized, face-to-face interviews conducted by trained researchers to ensure accuracy and completeness. The questionnaire will capture detailed information on participants’ demographic characteristics (sex, age, ethnicity, socioeconomic status, educational attainment, and family background), medical history and medication use, social support, cognitive function, psychological well-being, nutritional status, lifestyle and PA habits, fall risk, and pain status.

#### Primary outcome

The primary outcome is a composite sarcopenia Z-score adapted from previous sarcopenia and osteosarcopenia exercise trials that used standardized deficits in muscle mass, muscle strength, and physical performance to provide a continuous measure of sarcopenia severity [31, 43, 44]. In the present study, the score is aligned with the AWGS 2019 diagnostic domains and includes ASMI, HG, and SPPB [34]. These components were selected because they represent the three core domains of sarcopenia: muscle mass, muscle strength, and physical performance. SPPB was chosen as the physical-performance component because it integrates balance, gait speed, and chair-stand performance, which are particularly relevant to frail oldest-old nursing home residents.$$\begin{aligned} {\mathrm{Z}-\mathrm{s}\mathrm{c}\mathrm{o}\mathrm{r}\mathrm{e}}_{ \mathrm{M}} &=\frac{28.0-\mathrm{i}\mathrm{n}\mathrm{d}\mathrm{i}\mathrm{v}\mathrm{i}\mathrm{d}\mathrm{u}\mathrm{a}\mathrm{l} HG}{\mathrm{S}\mathrm{D} \mathrm{o}\mathrm{f} \mathrm{H}\mathrm{G}}\\ & \quad +\frac{9-\mathrm{i}\mathrm{n}\mathrm{d}\mathrm{i}\mathrm{v}\mathrm{i}\mathrm{d}\mathrm{u}\mathrm{a}\mathrm{l} SPPB}{\mathrm{S}\mathrm{D} \mathrm{o}\mathrm{f} \mathrm{S}\mathrm{P}\mathrm{P}\mathrm{B}}\\ & \quad+\frac{7.0-\mathrm{i}\mathrm{n}\mathrm{d}\mathrm{i}\mathrm{v}\mathrm{i}\mathrm{d}\mathrm{u}\mathrm{a}\mathrm{l} \mathrm{A}\mathrm{S}\mathrm{M}\mathrm{I}}{\mathrm{S}\mathrm{D} \mathrm{o}\mathrm{f} \mathrm{A}\mathrm{S}\mathrm{M}\mathrm{I}} \end{aligned}$$$$\begin{aligned} {\mathrm{Z}-\mathrm{s}\mathrm{c}\mathrm{o}\mathrm{r}\mathrm{e}}_{ \mathrm{F}}&=\frac{18.0-\mathrm{i}\mathrm{n}\mathrm{d}\mathrm{i}\mathrm{v}\mathrm{i}\mathrm{d}\mathrm{u}\mathrm{a}\mathrm{l} \mathrm{H}\mathrm{G}}{\mathrm{S}\mathrm{D} \mathrm{o}\mathrm{f} HG}\\ & \quad+\frac{9-\mathrm{i}\mathrm{n}\mathrm{d}\mathrm{i}\mathrm{v}\mathrm{i}\mathrm{d}\mathrm{u}\mathrm{a}\mathrm{l} SPPB}{\mathrm{S}\mathrm{D} \mathrm{o}\mathrm{f} \mathrm{S}\mathrm{P}\mathrm{P}\mathrm{B}}\\ & \quad+\frac{5.7-\mathrm{i}\mathrm{n}\mathrm{d}\mathrm{i}\mathrm{v}\mathrm{i}\mathrm{d}\mathrm{u}\mathrm{a}\mathrm{l} \mathrm{A}\mathrm{S}\mathrm{M}\mathrm{I}}{\mathrm{S}\mathrm{D} \mathrm{o}\mathrm{f} \mathrm{A}\mathrm{S}\mathrm{M}\mathrm{I}} \end{aligned}$$

The composite sarcopenia Z-score will be calculated separately by sex based on AWGS 2019. The three standardized deficit components will be summed, with higher scores indicating greater sarcopenia severity. Sex-specific baseline standard deviations will be used for standardization.Muscle mass (ASMI):ASMI will be measured using BIA with an InBody 770 device (InBody, Seoul, Korea). Participants will be instructed to remove shoes and socks, stand upright on the device, and maintain an upright posture with arms slightly abducted. Measurements will be performed under standardized conditions, including fasting for at least 4 h and emptying the bladder prior to assessment.Muscle strength (HG):HG will be measured using a calibrated Jamar hydraulic hand dynamometer (Patterson Medical, USA). Participants will be seated with the elbow flexed at 90°, forearm in neutral position, and wrist slightly extended. Each hand will be tested three times with a 1-min rest between trials, and the maximum value across all six trials will be recorded in kilograms.Physical performance (SPPB):Physical performance will be evaluated using the Short Physical Performance Battery (SPPB), which includes three components: GS test, 5STS test, and balance tests (side-by-side, semi-tandem, tandem). Each component will be scored from 0 to 4 according to standard criteria, with a total SPPB score ranging from 0 (worst) to 12 (best). Assessments will be performed by trained staff following standardized protocols, and participants will be allowed a single practice trial before formal measurements.

#### Secondary outcomes

Timed Up and Go Test.The Timed Up and Go (TUG) test will be used to assess functional mobility and fall risk [45]. Participants will be instructed to rise from a standard armchair (seat height 43–45 cm), walk at their usual pace for 3 m, turn around, return to the chair, and sit down.Balance Performance.Standing balance will be assessed using a modified Clinical Test of Sensory Integration for Balance on a Wii Fit Balance Board (Nintendo Co., Ltd., Kyoto, Japan), with center-of-pressure displacement derived from standardized stance conditions: 1) side-by-side, eyes open, 2) side-by-side, eyes closed and 3) semi-tandem, eyes open [46].Physical Activity and Sedentary Behavior patterns.PA and sedentary behaviour will be assessed using both objective monitoring and self-report. Objective data will be collected using a thigh-worn Fibion accelerometer (Fibion Inc., Jyväskylä, Finland) to characterize daily sedentary time and activity intensity [47, 48]. Participants will be asked to wear the device continuously 24 h/day over 7 consecutive days at each assessment time point [49, 50]. A valid assessment will require at least three valid days with a minimum predefined wear duration per day. Self-reported activity and sedentary behaviour over the preceding week will be assessed using the short form of the International Physical Activity Questionnaire (IPAQ-SF) [51].Neuromuscular Activation.Neuromuscular activation will be assessed using a wearable textile surface electromyography (sEMG) system (MSleeve, Myontec Ltd., Kuopio, Finland) [52–54]. Recordings from the tibialis anterior, gastrocnemius, and soleus muscles will be obtained during the GS test, 5STS test, TUG test, and standing balance assessment to examine exercise-related changes in lower-limb motor control. Predefined exploratory sEMG variables will include task-specific muscle activation amplitude, activation duration, and, where feasible, muscle co-activation patterns during functional tasks. Raw signals will be processed using standardized filtering, artefact removal, and normalization procedures specified before analysis.Biological Specimen Collection.At baseline and week 48, participants will be instructed to provide approximately 5 mL of saliva in a sterile collection tube, excluding froth. Prior to sample collection, participants will be asked to refrain from eating or drinking for 1–2 h to minimize contamination and ensure sample quality, following established saliva collection protocols [55]. All biospecimens will be stored at 4 °C in insulated containers for no more than two hours before transportation to the biochemistry laboratory at Zhejiang University for processing. Saliva samples will be centrifuged at 3,000 rpm for 10 min to separate cellular debris from the supernatant, following standard procedures for saliva sample preparation and biobanking [56]. The resulting fractions will be aliquoted into EP tubes. All processed samples will be stored at -80°C until omics profiling is conducted.Saliva-derived DNA will be extracted for telomere length measurement and DNA methylation analyses. Saliva provides a practical and non-invasive source of genomic DNA for large-scale population studies and has been widely used in aging research [57]. Telomere length is a well-established biomarker of cellular aging [58, 59], whereas DNA methylation profiles capture age-related epigenetic alterations and can be used to derive measures of biological aging, such as epigenetic clocks [60, 61]. Integrating these measurements provides complementary information on biological aging processes and may help elucidate mechanisms underlying age-related health outcomes and functional decline [57, 61].Questionnaire-Based Assessments.Questionnaire-based assessments will be used to evaluate cognition, mental health, sleep quality, frailty, health-related quality of life, functional independence, traditional Chinese medicine constitution, perceived physical activity needs, and adverse childhood experiences, using validated instruments including the CMMS, MoCA, GDS-15, GAD-7, PSQI, CFS, SF-36, ADL scale, CCMQ, and ACE-based indicators [62–71].Clinical Events and Care-dependency.Impaired mobility and sarcopenia-related functional decline are associated with adverse health outcomes, falls, increased healthcare utilization, and care dependency in nursing home residents [72, 73]. Therefore, clinical event records and care-dependency level will be collected through continued collaboration with the nursing home and verified using routine institutional records where available. Baseline clinical event records will capture pre-trial event history, including prior hospitalization or emergency transfer, falls, and injurious falls. During the 48-week intervention period, subsequent clinical events, including all-cause mortality and recorded cause of death, hospitalization or emergency transfer and corresponding reasons, falls, and injurious falls, will be continuously recorded and summarized at Week 12, Week 24, and Week 48. During the post-intervention follow-up period, the same clinical events will continue to be recorded and summarized at 1 and 2 years post intervention. Care-dependency level will be recorded at baseline, Week 12, Week 24, Week 48, and 1 and 2 years post intervention using routine nursing-care registration records [32].

### Feasibility and process evaluation

To complement the effectiveness evaluation, a mixed-methods feasibility and process evaluation will be conducted in accordance with Medical Research Council (MRC) guidance [39]. This component will examine implementation, mechanisms of impact, and contextual factors relevant to delivery within routine nursing home care.

Quantitative indicators will include recruitment, retention, attendance, fidelity, enjoyment, and adverse events, while qualitative data will be collected through interviews, focus groups, field observations, and researcher notes involving residents, caregivers, and administrators. The process evaluation will also explore participants’ and caregivers’ perceptions of the adherence support strategies, including supervision, feedback, incentives, social support and recognition. These data will be used to identify barriers and facilitators to implementation and to inform future refinement of the intervention and trial procedures.

#### Exercise intensity monitoring

Exercise intensity will be monitored to ensure that training is delivered within the prescribed moderate-intensity range. Perceived exertion will be assessed using the Borg Rating of Perceived Exertion scale, with a target range of 12–14. To complement this, heart rate will be measured once for each participant during the intervention period using a Polar OH1 + device (Polar Electro Oy, Kempele, Finland) as an objective spot-check of exercise intensity, with moderate intensity defined as 50–70% of the age-predicted maximum heart rate (HR _Max_ = 208 − 0.7 × age) [74].

### Statistical analysis

All analyses will follow the intention-to-treat (ITT) principle, including all randomized participants in their assigned groups regardless of adherence or withdrawal [75]. Data will be stored in a password-protected database and managed by designated research staff. Analyses will be performed by an independent statistician using R software (R Foundation for Statistical Computing, Vienna, Austria).

Baseline characteristics will be summarized using descriptive statistics. Continuous variables will be presented as mean ± SD or median [IQR], as appropriate, and categorical variables as frequencies and percentages. Baseline balance across groups and clusters will be descriptively assessed.

Primary and secondary continuous outcomes will be analyzed using linear mixed-effects models, with fixed effects for group, time, and group-by-time interaction, and adjustment for the baseline value of the corresponding outcome and relevant covariates where appropriate. Random intercepts for residential building clusters and participants will be included to account for cluster randomization and repeated measurements. The main intervention effect will be estimated from the group-by-time interaction, with Week 48 as the primary endpoint. Bonferroni-adjusted post-hoc comparisons will be conducted where appropriate. Binary or categorical outcomes, including adverse events, will be analyzed using generalized linear mixed models. Long-term clinical events and care-dependency records will be summarized descriptively by group, with exploratory cluster-adjusted analyses conducted if event numbers permit.

Model assumptions will be assessed using residual diagnostics, and transformations or robust methods will be considered if needed. Missing outcome data will be handled using multiple imputation under the missing-at-random assumption. Sensitivity analyses will compare the intention-to-treat results with per-protocol and complete-case analyses. Effect sizes will be reported as standardized mean differences for continuous outcomes and odds ratios for binary outcomes. Statistical significance will be set at a two-sided α = 0.05.

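### The mixed model set for all continuous outcomes does not suit the saliva markers, which have one follow-up visit: its interaction is either not identifiable or a less precise change-score contrast

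*Protocol article*

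**What the plan says.** Four statements in the protocol article bear on this.

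- **Scope of the model** (Statistical analysis): "Primary and secondary continuous outcomes will be analyzed using linear mixed-effects models". No exception is stated.
- **Terms of the model** (same section): "with fixed effects for group, time, and group-by-time interaction, and adjustment for the baseline value of the corresponding outcome". Also: "Random intercepts for residential building clusters and participants will be included to account for cluster randomization and repeated measurements".
- **Where the effect is read** (same section): "The main intervention effect will be estimated from the group-by-time interaction, with Week 48 as the primary endpoint".
- **Saliva schedule** (Outcome assessment): "biospecimens will be collected at baseline and week 48 only". Table 1 agrees, with sample collection marked at Week 0 and Week 48 only.

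The Abstract names saliva biological markers among the secondary outcomes, and they appear again under Secondary outcomes: "Saliva-derived DNA will be extracted for telomere length measurement and DNA methylation analyses". The other continuous outcomes are measured at baseline and at five later visits (Weeks 12, 24 and 48, and 1 and 2 years after the intervention).

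The article does not say whether the baseline value is a covariate only, a response row only, or both. The baseline adjustment points to the first. Reading the effect from an interaction with time points to the second.

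**The concern.** A model with time, group-by-time and a participant intercept needs at least two response rows per participant. The saliva markers have two measurements in all. If one of them is used as the baseline covariate, a single response row is left, and the term that is meant to carry the treatment effect has nothing to be estimated from.

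The analyst must then depart from the stated rule after the data exist, and the possible departures give different estimates and different precision. The Discussion looks to these markers for evidence on molecular adaptation to exercise, so how their between-arm contrast is obtained should be settled in advance.

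**Working it through.** The article gives no figure for the saliva analysis, so there is none to reproduce. The check takes each reading of the baseline value in turn.

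**Inputs.** From the article: 4 arms, 104 participants (26 per arm), 19 buildings, saliva at baseline and Week 48. Assumed: equal variances at the two visits (set to 1) and a baseline to Week 48 correlation r of 0.3, 0.6 or 0.8. The documents give no value of r. Variances below are for the contrast of two arms with n residents each and ignore the building effect.

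**Reading A: baseline as covariate only.** The fixed effects have 1 intercept + 3 group + 1 time + 3 group-by-time + 1 baseline = 9 columns. With Week 48 rows only, time is constant, so it duplicates the intercept, and each interaction column duplicates its group column. The rank is 5, and the time term and all three interaction terms are aliased. With one row per resident, the participant intercept cannot be separated from the residual. On simulated data with 19 buildings, R's lme4 refuses the fit because there are as many participant levels as observations.

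**Reading B: baseline as a response row.** With rows at Weeks 0 and 48 the rank is 9 of 9 and the model fits. The interaction is then the plain between-arm difference in change, whether or not the baseline covariate is also present. A covariate that is constant within a resident cannot alter a within-resident contrast in complete data. In one simulated data set the interaction and the change-score difference were both -0.2123, against -0.1807 from ANCOVA.

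Precision:

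- Change-score variance = 4(1 - r)/n
- ANCOVA variance = 2(1 - r²)/n
- Ratio of interval widths = √[2/(1 + r)]

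| r | 2/(1 + r) | Width relative to ANCOVA |
|---|---|---|
| 0.3 | 1.538 | 1.24 |
| 0.6 | 1.250 | 1.12 |
| 0.8 | 1.111 | 1.05 |

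**Reading C: baseline as both response row and covariate.** The contrast and its true variance are as in B, but the model's own standard error is wrong.

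- The pooled slope is b = (1 + r)/2.
- Residual variances are (1 - b)² at baseline and 1 - 2br + b² at Week 48.
- The residual covariance is (1 - b)(r - b), which is negative, so the participant variance estimate falls to 0. The lme4 run gave a singular-fit warning, as this implies.
- The model-based variance of the interaction is 4 × (mean residual variance)/n, against a true 4(1 - r)/n.

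| r | b | Residual variances (baseline, Week 48) | Mean | 1 - r | √(mean/(1 - r)) | SE too small by |
|---|---|---|---|---|---|---|
| 0.3 | 0.65 | 0.1225, 1.0325 | 0.5775 | 0.70 | 0.908 | about 9% |
| 0.6 | 0.80 | 0.0400, 0.6800 | 0.3600 | 0.40 | 0.949 | about 5% |
| 0.8 | 0.90 | 0.0100, 0.3700 | 0.1900 | 0.20 | 0.975 | about 2.5% |

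**Simulation.** With 4 arms of 26, no building effect and 3,000 runs per r, the true standard error was 1.22, 1.11 and 1.04 times that of ANCOVA. The model's own standard error under Reading C was about 10%, 4% and 2% too small. Both agree with the large-sample formulas. A run of only 200 data sets at r = 0.6 gave a loss of about 6% in place of 12%, but so few runs are noisy.

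**Other outcomes.** With baseline as covariate and Weeks 12, 24 and 48 as responses the rank is 13 of 13. With all five post-baseline visits it is 21 of 21. Non-identifiability is confined to the saliva markers.

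**The case against.** The strongest reply has four parts.

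1. **The model can be fitted.** This stands. A reader might infer that no estimate is possible for the saliva markers, but that is true only under Reading A. With baseline as a response row the model runs.
2. **The standard error need not be wrong.** This also stands. The clause on adjustment ends with a where-appropriate qualifier that may cover the baseline adjustment as well as the covariates. Baseline could then be a response and not a covariate. With equal variances, that two-row model reports the correct variance, 4(1 - r)/n. The loss against ANCOVA remains, but the understated standard error belongs to Reading C alone.
3. **A competent statistician would drop the inestimable terms.** That is plausible. The article ties the random intercepts to clustering and repeated measurements, and with one follow-up value there are no repeated measurements. The reduction leads to the Week 48 ANCOVA recommended here and loses no precision. Still, the article does not say so, and the change-score route is equally open to the analyst.
4. **The markers are exploratory, and an article leaves detail to the SAP.** Outcome assessment does group biospecimen collection with exploratory assessments that are done only when safe and tolerated, and this lowers the stakes. It does not remove the point. The Abstract and the Secondary outcomes section class the markers as secondary. The article also states a model, random effects and a source for the effect that cover them, so this is a stated rule that does not fit the stated schedule, not an omitted detail.

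**Conclusion.** The point holds as a minor one. For outcomes with a single follow-up visit, the prescribed group-by-time effect is either not identifiable (baseline as covariate) or equal to the change-score difference (baseline as response row). The second costs about 24%, 12% and 5% in interval width against ANCOVA at r = 0.3, 0.6 and 0.8. These figures rest on equal variances and on assumed correlations. If the markers are highly stable over 48 weeks, the loss is small.

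The documents do not support the inference that the saliva results must carry understated standard errors. That needs baseline on both sides of the model, which the article neither prescribes nor rules out. Nor do they support extending the identifiability problem to the primary Z-score or to other outcomes with several follow-up visits.

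**What to change.** Add one sentence to Statistical analysis. Continuous outcomes with a single follow-up visit (the saliva markers) are analysed as the Week 48 value on group and the baseline value of the same marker, with a random intercept for building and no time, group-by-time or participant terms. The effect is the adjusted Week 48 difference between arms.

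This model has 5 identifiable fixed-effect columns and fitted normally in the lme4 check. It needs no new data, visits or participants.
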